### Data Safety and Monitoring Board

Given the interventional nature of this trial, an independent Data and Safety Monitoring Board (DSMB) has been constituted in accordance with JIPMER’s DSMB guidelines to oversee participant safety and trial conduct. A DSMB charter was developed prior to trial initiation. The charter details the composition of the committee, minimum quorum requirements, frequency of meetings, the structure of meetings (open and closed sessions), and the procedures for documentation, communication, and reporting of recommendations.

The DSMB comprises 3 independent members: one expert from each of emergency medicine, internal medicine, and biostatistics. A quorum of 2 members is required for DSMB meetings. The study statistician will be responsible for presenting the interim efficacy analyses, and a consolidated summary of all AEs and SAEs will be submitted for DSMB review. The DSMB will periodically review accumulated safety and efficacy data, including a planned interim review after 50% enrollment in each treatment arm. Based on its evaluation, the DSMB may recommend continuation of the study without modification, protocol modification, or early termination of the trial. All DSMB recommendations will be formally communicated to the principal investigator, who will subsequently report them to the Institutional Ethics Committee.

An interim analysis will be conducted after enrollment of 50% of the planned sample size. The Haybittle-Peto stopping rule will be applied, with statistical significance for early termination defined as a *P* <.002 at the interim analysis stage. However, the final analysis will retain a 2-sided *α* level of .05.

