#### Analytical Statistics

The primary and secondary outcomes will be compared between the intervention and placebo groups using appropriate statistical tests. The proportion of patients achieving good neurological outcomes on day 28, as well as the proportion achieving good neurological outcomes at discharge, will be analyzed using the chi-square or Fisher exact test, with results expressed as relative risk estimates. Similarly, the comparison of in-hospital complications between the 2 groups will also use the chi-square or Fisher exact test, with relative risk used to quantify the effect size. For continuous outcomes, such as the duration of hospital stay, comparisons will be made using either the independent *t* test or the Mann-Whitney *U* test depending on data distribution, and the effect will be reported as an absolute difference between groups.

The primary efficacy analysis will be carried out by following the intention-to-treat principle. A per-protocol analysis will be performed as a secondary analysis. If there are missing data for the outcome at day 28, multiple imputation using chained equations will be used, based on the assumption that data are missing at random [26]. The primary analysis will also adjust for GCS stratification at baseline using a multivariable regression model. No adjustment for study site will be carried out, as all the sites have a similar profile with respect to available treatment and manpower. All statistical analyses will be carried out at a 5% level of significance, and a *P* value <.05 will be considered significant. For interim analyses alone, *P*<.002 will be applied, following the Haybittle-Peto stopping rule.

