### Sample Size

The sample size was calculated to detect a clinically meaningful difference in the proportion of patients achieving a good neurological outcome (GOS 4‐5) at day 28 between the dexamethasone and placebo groups. In our previous retrospective study, approximately 75% of near-hanging patients with altered sensorium who received steroids achieved a good neurological outcome [17]. Using these data, the expected event rate in the intervention group was assumed to be 75% while a favorable neurological outcome rate of 55% was assumed in the placebo group, corresponding to an absolute treatment effect of 20%.

The sample size for this superiority trial with a binary outcome was calculated using a 2-sided α of 0.05% and 80% statistical power. Sample size estimation was performed using the Sealed Envelope online sample size calculator for binary superiority trials [27]. The calculated sample size was 86 participants per treatment arm. To account for an anticipated 10% attrition rate due to loss to follow-up or protocol deviations, the sample size was inflated to 96 participants per arm, resulting in a total sample size of 192 participants.

The effect size was chosen as a pragmatic compromise between clinical relevance and study feasibility. Near-hanging with altered sensorium is an uncommon emergency presentation, and, based on patient admissions at the 3 study sites, 190 to 200 eligible patients were expected to be recruited during the planned study period. For detecting a smaller treatment effect, we will require a substantially larger sample size that will not be feasible within the available study period and funding. Despite this, an absolute improvement of 20% in favorable neurological outcomes was considered clinically important because such a benefit would be expected to substantially influence clinical practice, whereas failure to demonstrate a benefit of this magnitude would provide evidence against the routine empirical use of corticosteroids in this population.

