### Conclusions

The CHANGING trial seeks to address a major evidence gap in the management of near-hanging patients with altered consciousness, a population in whom corticosteroids are widely used despite limited supporting data. Through a rigorous multicenter, double-blind, placebo-controlled design, this study aims to determine whether dexamethasone improves neurological outcomes and safety. The results are expected to provide definitive evidence to guide clinical practice and inform future guidelines for managing near-hanging-associated cerebral injury.

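### Failing to show a 20-point benefit is called evidence against routine steroid use, but at the planned placebo rate a non-significant result alone does not exclude 20 points

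*Protocol article*

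**What the plan says.** The Sample Size section plans a superiority trial of 75% good outcome on dexamethasone against 55% on placebo, an absolute difference of 20 points, with "80% statistical power". That gives 86 per arm, raised to 96 for 10% attrition. The section concedes that a smaller effect would need a sample that is not feasible. It then closes by saying that "failure to demonstrate a benefit of this magnitude would provide evidence against the routine empirical use of corticosteroids in this population".

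Analytical Statistics compares the day-28 proportions by chi-square or Fisher exact test, "with results expressed as relative risk estimates", and declares significance at P<.05. An absolute difference is named there only for continuous outcomes such as hospital stay. Limitations grants that 20 points may be rather large but leaves the reading of a null result unchanged. The article's Conclusions add that "The results are expected to provide definitive evidence to guide clinical practice and inform future guidelines". That is a general closing statement and says nothing specific about a null result.

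**The concern.** A superiority test sized for a large effect answers one question: is the difference distinguishable from zero? Whether a 20-point benefit has been excluded is a different question, and the upper confidence limit answers it. The quoted sentence goes from the first to the second without mentioning that limit, directly after granting that smaller benefits are out of reach.

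The consequence would be practical. The Background section reports that 68% of near-hanging patients at one centre received steroids, and the trial hopes to inform guidelines. If a moderate real benefit gave a non-significant result and this sentence were applied as written, an inconclusive trial would be presented as evidence against use.

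**Working it through.** **Inputs.** Placebo 55%, dexamethasone 75%, 80% power, 86 evaluable and 96 randomized per arm (Sample Size). Two-sided 5% level: Analytical Statistics states "All statistical analyses will be carried out at a 5% level of significance", and the Data Safety and Monitoring Board section says "the final analysis will retain a 2-sided" level of .05. Sample Size prints the level differently ("calculated using a 2-sided α of 0.05% and 80% statistical power"), but only 5% gives 86, as step 1 shows.

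**1. The plan's own figure.** Unpooled normal approximation:

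n = (1.960 + 0.842)² × (0.75×0.25 + 0.55×0.45) / 0.20² = 85.36, rounded up to 86. Then 86/0.90 = 95.6, rounded up to 96.

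Both figures reproduce. At the printed 0.05% the same formula gives 203.2, that is, 204 per arm.

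**2. Largest non-significant result at the planned placebo rate.** The test is the uncorrected chi-square; the interval is d ± 1.96 × √[(p₁q₁ + p₀q₀)/n].

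- n = 86: 59/86 (68.6%) against 47/86 (54.7%), d = +14.0 points, P = .060. Half-width = 1.96 × √[(0.2154 + 0.2478)/86] = 14.4 points, so the 95% CI is -0.4 to +28.3.
- n = 96: 66/96 against 53/96, d = +13.5 points, P = .053, 95% CI -0.1 to +27.1.
- Newcombe intervals give upper limits of 27.7 and 26.6, so the choice of interval does not matter here.

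**3. Where the upper limit passes 20 points.**

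| n per arm | Table | Difference (points) | Upper 95% limit (points) |
|---|---|---|---|
| 86 | 47 vs 47 | 0 | 14.9 |
| 86 | 51 vs 47 | +4.7 | 19.4 |
| 86 | 52 vs 47 | +5.8 | 20.6 |
| 96 | 53 vs 53 | 0 | 14.1 |
| 96 | 58 vs 53 | +5.2 | 19.2 |
| 96 | 59 vs 53 | +6.3 | 20.2 |

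At 86 per arm, observed differences from about 6 to 14 points are therefore non-significant and still compatible with 20 points.

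**4. How often this would happen.** Binomial enumeration over all tables, placebo 55%, shown as n = 86 / n = 96:

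| True benefit | Non-significant | Of these, upper limit above 20 points |
|---|---|---|
| 20 points | 21% / 16% | 88% / 85% |
| 15 points | 47% / 43% | 79% / 75% |
| 10 points | 73% / 71% | 64% / 59% |
| 0 points | 94% / 95% | 23% / 20% |

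**5. Dependence on the placebo rate.** Upper 95% limit of the largest non-significant result, in points:

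| Placebo rate | n = 86 | n = 96 |
|---|---|---|
| 55% | 28.3 | 27.1 |
| 65% | 26.1 | 25.2 |
| 75% | 23.4 | 21.6 |
| 80% | 20.9 | 19.4 |
| 90% | 14.5 | 13.6 |

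The rates above 55% are a sensitivity range, not planning values.

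**The case against.** The best defence is that the sentence is rationale for the effect size, outside the Data Analysis Plan, and that it is narrower than it may look. A reader might infer three stronger things that the document does not support:

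- **That a wrong conclusion is pre-specified as an analysis rule.** Nothing in Analytical Statistics tells the analyst how to label a null result.
- **That non-significance is equated with no useful effect.** The text speaks of failing to show a benefit of that size, and of routine empirical use. For a drug with known harms, an unproven benefit can reasonably count against routine use.
- **That results will appear only as relative risks, with no absolute difference available.** The word only is not in the text, Summary Statistics reports categorical data as percentages, and a condensed article may leave further effect measures to the full protocol or analysis plan.

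The sentence is also partly true in a likelihood sense. At 55% placebo and 86 per arm, a non-significant result has probability 0.945 under no effect and 0.21 under a true 20-point benefit, a ratio of about 4.5. Against a 10-point benefit the ratio is only 0.945/0.727, about 1.3.

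Nor does every null result leave 20 points open. With no true effect at 55% placebo, 77-80% of non-significant trials exclude it. At 90%, the rate that Background gives for patients not given steroids (a comparison it describes as affected by selection), no non-significant result reaches 20 points.

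All of this limits the point without removing it. The inference is in print with no interval condition, and the concession in Limitations does not withdraw it.

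**Conclusion.** The concern holds in a limited form. On the protocol's own planning assumptions, failing to reach significance is not enough to argue against a 20-point benefit: the interval can extend to 27-28 points, and 16-21% of trials would miss a true 20-point benefit altogether. The size depends on the placebo rate. The problem is large at the planned 55%, modest at 75%, borderline at 80% and absent at 90%.

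The figures assume the chi-square test at two-sided 5%, Wald intervals, and an unadjusted comparison with 86 to 96 per arm. That range brackets complete cases and all randomized patients. The effect of the planned adjustment for baseline GCS stratum was not computed. The defect lies in one sentence about interpretation; the test and the sample size are not in question here.

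**What to change.** Replace the sentence in Sample Size with wording such as: Evidence against a 20-point benefit will be claimed only if the upper limit of the two-sided 95% CI for the day-28 risk difference in good outcome (dexamethasone minus placebo) is below 20 points; a non-significant result whose interval includes 20 points will be reported as inconclusive.

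In Analytical Statistics, state that this risk difference and its 95% CI will be reported beside the relative risk, because the 20-point target is on the absolute scale. If the full protocol or analysis plan already provides for this, a cross-reference is enough.

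The change costs one sentence and one extra estimate. Design, data collection, test and sample size stay as they are. With 3 patients enrolled at submission (Results), the rule can still be set well before any outcome comparison. The real price is that some null results will have to be called inconclusive. Even an interval that excludes 20 points speaks only to a benefit of that size and not to smaller ones.

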### Protocol Amendments

Several amendments were made to the study protocol to improve feasibility, clarity, and participant safety. The current version of the protocol is version 1.5, dated July 1, 2025. The inclusion window was extended from 24 hours to 48 hours following a hanging attempt, as several otherwise eligible patients were referred from nearby districts and presented beyond the original 24-hour period, leading to the loss of potential participants. This change was implemented to enhance recruitment, given the relatively low number of hanging cases.

The exclusion criterion related to corticosteroid use was corrected to address a typographical error: the intended exclusion dose was clarified as 20 mg of dexamethasone or an equivalent corticosteroid dose, rather than 24 mg. Additional exclusion criteria were introduced to explicitly exclude patients with a definite indication for, or contraindication to, steroid therapy, and to clearly state the exclusion of patients who did not provide informed consent.

Amendments were also made to the criteria for discontinuation of the study drug. While the originally planned duration of study drug administration was 3 to 5 days, a predefined tapering or early discontinuation strategy was introduced for patients who achieved rapid neurological recovery (GCS score of 15/15), particularly if this occurred by day 1, to minimize unnecessary drug exposure and ensure patient safety. Furthermore, mandatory permanent discontinuation of the study drug was specified for participants who developed a definite indication for or contraindication to steroid therapy during the trial period. All amendments were made to enhance patient safety, improve protocol clarity, and address issues encountered during recruitment.

## Results

The study commenced in October 2025 and is planned to be completed by May 2028. A total of 192 participants will be recruited. At the time of manuscript submission, patient recruitment had been initiated at the primary center (JIPMER), where 16 patients had been screened and 3 patients had been enrolled. The remaining 2 participating centers are in the process of completing the necessary regulatory and logistical requirements to initiate recruitment. Data analysis will be conducted, and final results will be reported after the conclusion of the study. The protocol has been developed in accordance with the SPIRIT 2013 recommendations, and the final trial results will be reported in accordance with the CONSORT (Consolidated Standards of Reporting Trials) 2010 statement [28].

## Discussion

### Expected Findings

The hypoxic-ischemic brain injury seen in near-hanging is associated with substantial mortality and long-term neurological disability despite advances in critical care [5,7]. The secondary brain injury determines the neurological outcome despite prompt resuscitation. Jugular venous obstruction results in flow stagnation, leading to cerebral hypoxia, which may be the initial event in hanging. Excessive cerebral perfusion of an already hypoxic brain following relief of obstruction may also contribute to cerebral edema [5,21]. Currently, there is no guideline-directed therapy for improving neurological recovery in these patients, and the management is only supportive [21].

The pathophysiology of cerebral edema in near-hanging is poorly understood. The following mechanism is proposed for hypoxia-induced cerebral edema at high altitudes and in traumatic brain injury. Hypoxia at altitude elicits neuro-hormonal (VEGF, nitric oxide, reactive cytokines, and free radicals) and hemodynamic responses, resulting in hypoxia-induced cerebral vasodilation leading to over perfusion of microvascular cerebral beds. This leads to intracranial hypertension with elevated capillary pressure and capillary leakage. The disruption of the blood-brain barrier from these stressors leads to subsequent vasogenic cerebral edema. Another theory is that hypoxia induces free radical formation, causing damage or failure of the Na+/K+ATPase pump with resultant astrocyte swelling from osmotic-oxidative stress and subsequent cytotoxic edema [29]. Similarly, hypoxia can cause cerebral edema in hanging patients. Steroids are indicated to treat vasogenic cerebral edema, whereas osmotic agents such as mannitol and hypertonic saline are preferred for the treatment of cytotoxic edema. The rationale for using dexamethasone in hanging-related cerebral edema is that it has demonstrated clinical benefit in conditions characterized predominantly by vasogenic cerebral edema, including bacterial meningitis and brain tumors [30].

There is very limited evidence for the use of corticosteroid therapy in near-hanging. The existing literature is predominantly retrospective and comprises narrative reviews with several methodological limitations [8,18,31]. Our previous retrospective study demonstrated frequent empirical use of corticosteroid therapy in routine clinical practice but could not establish treatment efficacy because of its observational design [17]. No randomized controlled trials are currently available on steroid therapy specifically for near-hanging patients. However, there are studies available on steroid therapy for traumatic brain injury that closely resemble the type of brain injury seen in near-hanging cases. The MRC CRASH trial studied corticosteroids in patients with head injury, finding a higher death rate in those given corticosteroids (25.7%) compared with placebo (22.3%). This suggests that corticosteroids should not be used routinely to treat head injuries [19].

A narrative review by Kannamani et al [21] on near-hanging described head-end elevation, sedation, maintaining normocapnia (PaCO_2_ of 30‐35 mm Hg), and osmotic diuretics (hypertonic saline, mannitol) as management for cerebral edema and did not include steroid therapy in the management. A short review on steroid therapy in near-hanging patients reported that there is no evidence for or against the use of steroids in this situation [32].

Our CHANGING trial has been designed to address this evidence gap through a multicenter, randomized, double-blind, and placebo-controlled design. Random allocation and blinding of participants, treating clinicians, and outcome assessors are expected to minimize selection and assessment bias [22,28]. The study is conducted in 3 different tertiary care hospitals, which will improve external validity by including patients across diverse intensive care settings. To enhance the reliability of the study findings, the study follows a standardized treatment protocol, predefined neurological outcome, and systematic AE reporting [22].

Our trial uses patient-centered functional outcome as the primary endpoint. The assessment of neurological recovery using the Glasgow Outcome Scale at day 28 reflects clinically meaningful recovery rather than just a physiological improvement and has been widely used in studies of traumatic brain injury [24,33]. Simultaneous assessment of AEs will aid in balancing potential neurological benefits against complications related to corticosteroids, including hyperglycemia, secondary infections, hypokalemia, and gastrointestinal bleeding [34].

### Limitations

There are a few anticipated limitations to consider; this trial is being conducted at 3 tertiary care centers in India, which may limit the generalizability of the findings to other public and private hospitals or to international populations. The sample size calculation assumed a 20% absolute difference between the treatment groups, which may be considered relatively high. This assumption was made to ensure feasibility within the constraints of the 3-year study period, available funding, and the limited number of near-hanging cases, and it represents a pragmatic compromise between feasibility and statistical power. Short-term follow-up (28 d) is also a limitation.

### Conclusions

The CHANGING trial seeks to address a major evidence gap in the management of near-hanging patients with altered consciousness, a population in whom corticosteroids are widely used despite limited supporting data. Through a rigorous multicenter, double-blind, placebo-controlled design, this study aims to determine whether dexamethasone improves neurological outcomes and safety. The results are expected to provide definitive evidence to guide clinical practice and inform future guidelines for managing near-hanging-associated cerebral injury.
